**Methods/Design:**

Three-arm, randomized controlled clinical trial implemented in the primary care setting, with a duration of 40 weeks (16 weeks intervention and 24-week follow-up).

Adults aged 30 to 55 years with metabolic risk factors will be randomized into three intervention groups: 1) aerobic interval training (16 supervised training lessons) plus a healthy lifestyle counselling programme (6 group and 3 individual meetings); 2) low-to-moderate intensity continuous training (16 supervised training lessons) plus the same counselling programme; or 3) the counselling- programme without any supervised physical exercise.

The main output variables assessed will be risk factors for metabolic syndrome (waist circumference, blood pressure, and levels of plasma triglycerides, high-density lipoproteins and glucose), systemic inflammation, cardiorespiratory fitness, physical activity and sedentary behaviour, dietary habits, health-related quality of life, self-efficacy and empowerment. Economic factors will also be analysed in order to determine the cost-effectiveness of the programme. These variables will be assessed three times during the study: at baseline, at the end of the intervention, and at follow-up. We estimate to recruit 35 participants per group.

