#### Plasma microRNA determination

We will analyse miR-197, miR-23a, miR-509-5p, miR-130a-b, miR-195, miR-27a and miR-320, which are known to be deregulated and associated with features of metabolic syndrome. Targeted microRNA will be determined after its extraction from blood samples, following the instructions provided with the MagMax mirVana RNA isolation kit. In addition, any microRNA will be quantified by a specific TaqMan Advanced miRNA assay.

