#### Untargeted and targeted metabolomics and lipidomics

Metabolomics and lipidomics will be performed after the extraction of metabolites and lipids from plasma/serum at the baseline and final stages of the experiments. Metabolites and lipids will be separated by UPLC and detected by QTOF and TQP, depending on the procedure. Species identification will be performed via the PCDL database of Agilent Technologies, which uses retention times in a standardized chromatographic system as an orthogonal searchable parameter to complement accurate mass data (accurate mass retention time approach). In both cases, the SMPDB database [38, 39] will be used for querying metabolites obtained from the HMDB search, using a 0.05 Da M.W. tolerance and the Metaboanalyst platform [40, 41] for the determination of differential features.

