#### Statistical methods

An initial overview analysis will be carried out to detect any errors and to check the data for normality (Shapiro-Wilks test), this being done for all participants and intervention groups.

Intention-to-treat (ITT) analysis will be performed for all recruited participants who complete the baseline assessment, regardless of whether they subsequently complete the whole protocol. Missing outcome values will be replaced by data registered in the previous assessment using the last observation carried forward (LOCF) technique.

For the baseline comparison of groups we will use the chi-square test (or Fisher’s exact test) for categorical data and the analysis of variance (ANOVA) (or Kruskall-Wallis test) for quantitative data (continuous or ordinal). If significant differences are detected we will use Student’s *t*-test (or Mann–Whitney test) for each pair of groups.

For the analysis of the *intervention* effect two time frameworks will be established: efficacy (at the end of the intervention: t1) and durability (at 24-week follow-up: t2). Change will be calculated as the change from baseline values, both as absolute values and as a percentage adjusted to baseline values. We will adjust repeated measures techniques to study the general behaviour of the outcomes in the follow-up.

Continuous variables will be expressed as mean and standard deviation (SD). Effect size will be estimated as the mean standardized difference between the mean of each group divided by the pooled standard deviation. In accordance with Cohen’s criterion [54], values of 0.2–0.5 represent small differences, 0.5–0.8 moderate differences and >0.8 large differences. Categorical variables will be expressed as counts (n) and percentages (%), unless otherwise specified.

All analyses will be conducted using the Statistical Package for the Social Sciences (SPSS) v17 (SPSS Institute Inc., IL, USA) and the level of significance will be set at *p* < 0.05.

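### The article's one significance rule, p < 0.05 for all analyses, is left as the only threshold for an untargeted omics screen, where it would flag about 5% of null features per contrast

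*Protocol article*

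**What the plan says.** The last sentence of Statistical methods in the protocol article covers software and significance together. It begins "All analyses will be conducted using the Statistical Package for the Social Sciences (SPSS) v17" and ends "the level of significance will be set at *p* < 0.05". The article describes no adjustment for multiple testing and sets no analysis apart as exploratory.

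The section headed "Untargeted and targeted metabolomics and lipidomics" names other software for picking features, the "Metaboanalyst platform [40, 41] for the determination of differential features". It states neither a significance threshold nor the number of features expected.

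The microRNA section lists a short targeted panel: "We will analyse miR-197, miR-23a, miR-509-5p, miR-130a-b, miR-195, miR-27a and miR-320". That is 7 entries, or 8 if miR-130a and miR-130b count separately.

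Table 3 schedules both the metabolome-lipidome and the microRNA measurements alongside the other outcomes. The design has three arms.

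**The concern.** A per-test level of 0.05 suits a small number of named comparisons. An untargeted screen tests a large set of features, few of which may truly respond, and at that level the number of chance findings grows in proportion to the size of the set. If the stated rule is carried into the screen, the resulting list of metabolites and lipids could be mostly noise, and nothing in the article would tell the reader so.

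The two sections also do not fit together. One says that all analyses are done in SPSS, and the other does the feature selection elsewhere. An analyst cannot tell from the article whether the 0.05 rule goes with the omics or stays behind with SPSS.

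**Working it through.** The article gives no error rate or feature count for the omics, so there is no figure of its own to reproduce.

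**Inputs**
- Level per test: 0.05 (Statistical methods).
- Adjustment: none stated.
- Number of untargeted features, m: not given. Assumed values are 100, 500 and 2,000.
- MicroRNA panel: m = 7 or 8 (microRNA section).

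**1. Expected false positives per contrast, no true effects.** The formula is m × 0.05, and it does not need independence between features.

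| m | Expected false positives |
|---|---|
| 100 (assumed) | 100 × 0.05 = 5 |
| 500 (assumed) | 500 × 0.05 = 25 |
| 2,000 (assumed) | 2,000 × 0.05 = 100 |
| 7 microRNAs | 7 × 0.05 = 0.35 |
| 8 microRNAs | 8 × 0.05 = 0.40 |

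**2. Chance of at least one false positive per contrast.** The formula is 1 − 0.95^m, which assumes independent tests.
- m = 7: 1 − 0.95^7 = 0.30.
- m = 8: 1 − 0.95^8 = 0.34.
- m = 100: 1 − 0.95^100 = 0.994.

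**3. Illustration with sparse true effects.** Assume 500 features, 10 of them truly changed.
- Expected false findings: 490 × 0.05 = 24.5.
- At an assumed 80% power, 10 × 0.8 = 8 true findings, so the false share is 24.5 / 32.5 = 75%.
- At an assumed 50% power, 10 × 0.5 = 5 true findings, so the false share is 24.5 / 29.5 = 83%.

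**4. Does the rule reach the omics?** The two statements side by side:
- Statistical methods: all analyses, SPSS v17, p < 0.05.
- Omics section: Metaboanalyst, no threshold.

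If the word all is taken literally, 0.05 covers the omics, but the software statement is then contradicted. If the sentence covers only the SPSS analyses, the omics have no threshold. On either reading the two sections need reconciling.

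**The case against.** The strongest reply is that the article never says 0.05 is the per-feature cut-off. The level shares a sentence with SPSS, and feature selection is assigned to another platform. Nor does the article use the word unadjusted: a 0.05 level is compatible with adjusted p-values, or with a 5% false discovery rate. Feature-level error control is also a detail that an article may leave to the full protocol or the analysis plan. This stands in part: the reach of the rule to the omics is a literal reading, not an explicit assignment. It does not remove the point, because the complaint is not that a detail is absent. The article fixes one threshold and one software package for everything, and another section does not fit that rule.

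A reader might also infer four stronger things that the article does not support.

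- **Many false positives among the microRNAs.** The panel is short, targeted and chosen in advance. About 0.4 are expected per contrast.
- **Totals six times larger, from three pairwise contrasts at two time points.** Statistical methods describes pairwise tests only for the baseline comparison. Intervention effects are to be studied as change from baseline and with repeated-measures techniques. The omics section speaks of baseline and final stages, whereas Table 3 ticks three visits.
- **A near-certain false positive across all microRNA tests.** Multiplying over contrasts and visits as if they were independent does not fit this design. Pairwise contrasts among three arms are linearly dependent, changes at t1 and t2 share a baseline, and a missing t2 value is filled from the previous assessment.
- **Omics findings presented as the mechanism of the exercise effect.** No section says so.

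**Conclusion.** The point holds in a limited form. The only threshold in the article is 0.05, stated for all analyses without multiplicity control, and the untargeted screen has none of its own. Applied per feature, that rule flags about 5% of null features in each contrast: 5, 25 or 100 for 100, 500 or 2,000 features. Those counts are assumptions, and the size of the problem scales directly with them. For the microRNAs the expected number is 0.35 to 0.40 per contrast, with a 30% to 34% chance of at least one if the tests are independent.

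It would be wrong to conclude that the trial's main results are at risk. Metabolomics, lipidomics and microRNA are not named in the primary or secondary aims in the Background, nor among the main output variables in the Abstract. The point concerns how far the screening output can be trusted, and it is worth correcting because the correction is nearly free.

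**What to change.** Amend Statistical methods and the omics section so that they agree:

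1. State that the p < 0.05 rule and the SPSS statement do not govern the metabolomic, lipidomic and microRNA analyses.
2. Declare metabolomic and lipidomic features at a Benjamini-Hochberg false discovery rate of 5% within each platform and contrast.
3. Apply the same adjustment across the microRNA panel within each contrast.
4. Label all of these analyses exploratory.

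This takes a sentence or two and a standard adjustment, with no change to data collection or sample size. The downside is that fewer features will be declared, and some true but weak effects will be missed.

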### Risk and burdens

The main expected difficulties are a low adherence rate and the impossibility of blinding the intervention to participants and researchers. However, we will seek to minimize the former by individualizing attention (providing and discussing written feedback reports) during the implementation phase and the latter by blinding researchers to the group to which individuals were allocated.

## Discussion

In its 2008–2013 action plan the WHO [55] states, among others, the following aims: a) the promotion of interventions for the prevention and control of the main modifiable risk factors for non-communicable disease, b) the implementation of actions to help individuals to enhance their self-efficacy, improving literacy and providing tools for self-control, and c) the promotion of research to establish the cost/efficacy relationship of these interventions. We believe that with our study design we focus on these key aspects.

Current evidence indicates that AIT may be a valuable physical exercise strategy in terms of improving cardiac and metabolic risk status, functional capacity and quality of life [12, 18, 20]. AIT has demonstrated consistently better results than TCT when it comes to improving VO_2max_. Given that the VO_2max_ is associated with premature mortality and cardiovascular risk [56] the potential ability of AIT to improve this parameter is, from the health perspective, a promising finding. However, although the efficacy of AIT to induce physiological improvements in a well-controlled research environment is no longer in doubt, questions remain regarding the extent to which its benefits are transferable to a less-controlled clinical environment [21]. A further issue is that the evidence regarding the effectiveness of more traditional programmes for promoting physical activity is also inconsistent [57]. This study aims to address this issue by evaluating the effectiveness of AIT versus TCT (both concomitant with lifestyle counselling) as a primary care intervention for the management of metabolic syndrome risk factors in low-active adults presenting one or more of such factors.

A major strength of our study is its design, which will shed light on the extent to which 1) an AIT programme is a viable tool for implementation in the primary care setting, and 2) whether individuals will remain compliant with the programme in the medium term without supervision. Our study is unique as, unlike other AIT studies, it considers not only the physical exercise aspect but also links this to strategies for behaviour change and empowerment of individuals. According to Biddle [58], structured physical exercise programmes led by competent professionals are more effective at encouraging sedentary individuals to become more active than are poorly structured programmes or programmes that are self-administered at home. However, in order to achieve long-lasting and successful outcomes these programmes need to include psychological goals and strategies (mood, literacy, self-efficacy, social integration) focused on behaviour change. In this regard, our study includes a lifestyle counselling intervention that incorporates strategies for promoting regular physical activity, minimizing sedentary behaviour, improving dietary habits and enhancing participants’ self-efficacy. To our knowledge, this would be the first study in Spain to analyse the effect of AIT in conjunction with strategies to promote behaviour change and empower participants.

Another important feature of our study is that, alongside the assessment of changes in traditional metabolic risk factors after the intervention, we will also examine its effect on systemic inflammatory status [5, 59], cardiorespiratory fitness, self-efficacy for physical activity and dietary habits, empowerment related to health and health-related quality of life, as well as changes in physical activity levels, sedentary behaviour and dietary habits.

As noted by Marrugat et al. [60], the most efficient way of controlling the economic burden of public health and the mortality rates associated with cardiovascular diseases is to reduce their prevalence. One of the strategies for doing so could be the implementation of interventions designed to promote a healthy lifestyle, but in order to establish public health priorities it is first necessary to determine the cost effectiveness of such interventions. Consequently, the present study, in addition to examining the effects on physiological, psychological and behavioural parameters, will also assess the economic impact of the intervention.

The results of this study will provide insight into the immediate and medium-term effects on metabolic risk and lifestyle of the combination of AIT with a multidisciplinary behavioural intervention. If effective, the proposed intervention would provide both researchers and practitioners in this field with a platform on which to develop similar intervention programmes for tackling the repercussions of an unhealthy lifestyle.

## Abbreviations

AIT: Aerobic Interval Training
ANOVA: analysis of the variance
BMI: Body Mass Index
BP: Blood Pressure
cMSSy: Metabolic Syndrome Risk Score
COU: counselling
CPM: Counts Per Minute
DBP: Diastolic Blood Pressure
ECG: Electrocardiogram
EQ VAS: EQ Visual Analogue Scale
EQ-5D: EQ-5D questionnaire
FFC: Food Frequency Questionnaire
HbA1c: Glycated haemoglobin
HC: Hip Circumference
HDLc: High Density Lipoprotein cholesterol
HEI: Healthy Eating Index
HES: Health Empowerment Scale
HIIT: High-Intensity Interval Training
HRQoL: Health Related Quality of Life
IDIAP: Primary Care Research Institute-Jordi Gol
IL-6: interleukin-6
ITT: Intention-To-Treat
LDLc: Low Density Lipoprotein cholesterol
LOCF: Last Observation Carried Forward technique
LPA: Light Physical Activity
miRNA: microRNA
MVPA: Moderate-to-Vigorous Physical Activity
PA: Physical Activity
PCDL: Personal Compound-Database and Library
QALYs: Quality Adjusted Life Years
QTOF: Quadrepole Time-Of-Flight
RER: Respiratory Exchange Ratio
RNA: Ribonucleic Acid
RPE: Ratings of Perceived Exertion
Rpm: Revolutions per minute
SBP: Systolic Blood Pressure
SMPDB: Small Molecule Pathway Database
TC: Total Cholesterol
TCT: Traditional Continuous Training
TG: Triglycerides
TQP: Triple-Quadre-Pole
UPLC: Ultra Performance Liquid Chromatography
VO_2_: Oxygen uptake
VO_2max_: Maximal Oxygen uptake
VO_2peak_: Peak Oxygen uptake
WC: Waist Circumference
WHO: World Health Organisation
WtHr: Waist-to-Hip ratio.
